#### Short-form MPQ

In this study short-form MPQ of 15 questions^27^ is used, which distinguishes between the sensory–discriminatory and the affective and emotional aspects of the pain experience. Participants are asked to estimate their pain intensity and to describe their pain in predetermined words. They fill in the MPQ on all three measurement occasions.

#### RAND-36

RAND-36 is a quality-of-life instrument^28^ that aims to measure health-related quality of life, that is, physical, mental and social well-being, not just the absence of illness. The estimation instrument consists of 36 questions of various kinds, for example, on general health, activity, physical health, emotional problems and pain. RAND-36 is filled in by the participant on all three measurement occasions.

#### Patient Global Impression of Change

PGIC^35^ evaluates participants’ experience of the treatment, that is, the substance given. Participants tick the box that most closely describes the change that they are experiencing. The PGIC is completed by the participant after the injection treatment has been concluded at 12 weeks and at the follow-up 12 weeks later. PGIC is directly translated in its entirety from English by the research group.

#### Cobalamin/p

Cobalamin/p levels are taken on three occasions. The first measurement, baseline, rules out a vitamin B_12_ deficiency (according to the accepted reference values). A second measurement is performed at 12 weeks on completion of treatment in order to monitor the participants’ level of cobalamin/p just after the end of the injection treatment. The final measurement is 12 weeks after the end of intervention.

#### Qualitative in-depth interview

In order to obtain a deeper understanding of women’s perceived experiences, in-depth interviews with both compliant and non-compliant participants from both groups will be performed in connection with the third measurement session. The aim is to describe the women’s lived experiences of pain, health, suffering and well-being. The interviews will be conducted by the trial manager, recorded, transcribed and later analysed using an RLR (Reflective Lifeworld Research) approach.^24^

### Sample size

In order to obtain an adequate sample size, a power analysis was performed based on results from a previously published study^29^ in which women with fibromyalgia underwent the same stimulation procedure with the cold pressor test. Account is taken here of the SD shown and compensation for any placebo effects. Based on these results, the expected effect difference is estimated at 20 s with an SD of 20 s between the two groups after 12 weeks of treatment with mecobalamin (vitamin B_12_)/placebo. Using a two-sided t-test for two independent groups with a power of 80% and 5% significance level, it was calculated that each group would consist of 16 participants. In order to compensate for any loss, 20 participants per group are therefore included. The study continues until 40 participants have been included and have completed the study.

### Randomisation and allocation concealment

Participants are randomised into two groups, the placebo group or the treatment group, each consisting of 20 participants either receiving mecobalamin (vitamin B_12_) or placebo. An independent statistician generates a randomisation list by random distribution of processing in blocks (1:1) in a computerised statistics programme (STATA, version 17.1). Participants are randomised according to the list by the chief examiner opening closed randomisation envelopes in consecutive order. Based on each randomisation envelope, the chief examiner registers in and signs the injection retrieval protocol as to which substance the participant will receive. The participants’ randomisation number is recorded in the journal. Only the chief examiner has access to randomisation envelopes and injection retrieval protocols, which are kept locked.

When the third measurement session has been completed, the trial manager contacts the chief examiner who has the randomisation list.

The chief examiner breaks the code and notifies the participant with a letter of given treatment. The code is broken at this time because it cannot be considered ethical that the participant does not find out about the treatment given, especially if the participant believes that the treatment has helped. If the participants have received mecobalamin and wish to continue, they are recommended to contact their health centre for continued mecobalamin treatment. The letter will contain the contact information of the trial manager and the chief examiner if the health centre doctor wishes to contact them. The trial manager is still unaware of what the individual participant received until the study is completed. If the code needs to be broken for an individual participant before the third measurement session has been completed, there is a code breaking envelope that may be used by the chief examiner in cases of emergency.

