## Methods and analysis

### Study design

The study is an academic randomised, placebo-controlled, single-blind clinical trial using parallel groups. Participants are individually randomised to intervention or control group (placebo) in a 1:1 allocation. In order to broaden and deepen the understanding of the lived experience, an interview will be conducted applying a phenomenological approach on a lifeworld theoretical basis, reflective lifeworld research (RLR) approach.^24^

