### Intervention and placebo

The active substance of vitamin B_12_ given in the study is 2 mL mecobalamin (5 mg/ml), administered intramuscularly.^25^ Placebo substance is 2 mL sodium chloride (9 mg/ml), isotonic solution for parenteral use (Baxter) intramuscularly.^26^ All participants are informed that their urine may turn red, which may occur during mecobalamin injections.

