#### Cold pressor test

The cold pressor test^29–31^ is measured in number of seconds the participant leaves her hand in the low-temperature water of 5°. Evaluation variables from the cold pressor test become pain threshold (when it starts to hurt) and tolerance time, that is, how long the participant endures the pain. The participants end the test by raising their hands when they can no longer stand it or when the set end time of 3 min has elapsed.

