#### Pressure algometry test

The pressure algometry test^32 33^ generates a mechanical pressure against specific points on the body: trapezius (shoulder), epicondyle (elbow), gluteal (outside the gluteal muscles) and medial knee (inside of the knee), which are all accepted in the diagnosis of fibromyalgia. Pressure algometry tests are measured in kilopascal. The trial manager interrupts the mechanical pressure when the participant expresses pain.

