#### Numerical Rating Scale

The participants rate their pain intensity on NRS^34^ in connection with the cold pressor test when the participant takes her hand from the water, after 1 min and finally after 3 min. The participants estimate their pain intensity on a scale (NRS) from 0 to 10, where 0 corresponds to no pain at all and 10 corresponds to the worst possible pain. Pain rating is measured in the same way after the pressure algometry test.

The influence of expectation, desire for pain relief and pain variability will be measured before each injection using the same NRS as used for pain ratings. Ratings of expected pain levels will be obtained by asking patients ‘What level of pain do you expect when this treatment starts to have an effect?’ The NRS scale is anchored at the left by the descriptors ‘no pain sensation’ and at the right by ‘the most intense pain sensation imaginable’. Ratings of desired pain relief will be obtained by asking patients ‘How strong is your desire for pain relief?’ The question will be anchored by the descriptors ‘0=no desire for pain relief’ and ‘10=the most intense desire for pain relief imaginable’. Ratings of pain variability will be obtained by asking the participants their average pain intensity that week. These scales have been validated and used in previous studies.^36–40^

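### The code-break letter gives doctors the trial manager's contact details while the plan says the trial manager stays unaware of treatment, and that role is still testing other women

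*Protocol article*

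**What the plan says.** The protocol article (Study design) calls the trial single-blind: "The study is an academic randomised, placebo-controlled, single-blind clinical trial using parallel groups". Its section Randomisation and allocation concealment goes further and states a blind for one named role, the trial manager: "The trial manager is still unaware of what the individual participant received until the study is completed".

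The same section provides for a code break woman by woman. Once her third measurement is done, the chief examiner breaks her code and writes to tell her what she received. Those who had mecobalamin and want more are pointed to their health centre. On that letter the article says: "The letter will contain the contact information of the trial manager and the chief examiner if the health centre doctor wishes to contact them".

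Other duties of the trial manager are spread over several sections:
- takes the first contact from prospective participants (Study setting and sample);
- checks eligibility together with a coexaminer (Measurements);
- runs the algometer: "The trial manager interrupts the mechanical pressure when the participant expresses pain" (Pressure algometry test);
- conducts the interviews at the third visit (Qualitative in-depth interview).

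Allocation is 1:1 in blocks, with no block size given. Recruitment began on 6 February 2019 and is expected to finish in 2024 (Ethics and dissemination).

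**The concern.** The letter creates a channel to the one person whose ignorance of treatment the next sentence asserts. Only mecobalamin women who wish to continue are sent to a doctor, so a call asking about continuation is revealing even if the doctor never states the arm.

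The disclosed woman has finished. What is at stake is the women who follow. The trial manager stops the algometer when a woman expresses pain, which leaves room for judgement, and also leads the interviews. An assessor who begins to learn which finished women had the active drug may form expectations about it. Because allocation is in blocks, that assessor may also gain some information on the arms of women still under test. The single-blind label does not dispose of this, since the plan explicitly promises that this role stays unaware.

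**Working it through.** The plan gives no figure on this point, so the check has three parts: the statements side by side, the overlap in time, and what one disclosed arm reveals.

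**1. Statements side by side.** (a) The letter names the treatment. (b) Women on mecobalamin who wish to continue go to a health-centre doctor. (c) That doctor is given the trial manager's details as well as the chief examiner's. (d) The trial manager remains unaware until the study is completed. If the route in (c) is used for the purpose in (b), (d) is no longer true for that woman.

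**2. Are others still under test when letters go out?** Inputs: 40 women (Sample size); 24 weeks from start to last visit (Measurements; Adverse events); recruitment from February 2019 into 2024, so about 5 to 6 years. Assumption: evenly spaced entry.

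Interval between entries = years × 52 / 40, which is 6.5 weeks (5 years) to 7.8 weeks (6 years). Entries in any 24 weeks = 24/6.5 = 3.7 to 24/7.8 = 3.1.

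| Order of entry | Entry (week) | Week-12 test | Third visit |
|---|---|---|---|
| 1 | 0 | 12 | 24, then code broken |
| 2 | 6.5–7.8 | 18.5–19.8 | 30.5–31.8 |
| 3 | 13.0–15.6 | 25.0–27.6 | 37.0–39.6 |
| 4 | 19.5–23.4 | 31.5–35.4 | 43.5–47.4 |

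When the first woman's code is broken, the next three all have their third visit ahead, and the third and fourth also have their week-12 test ahead. Recruitment was in fact delayed by the pandemic, so actual spacing will have been uneven.

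**3. What one disclosed arm says about a block-mate.** In a balanced block of size B, once one member's arm is known, B/2 of the remaining B − 1 places are in the opposite arm:

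P(opposite) = (B/2)/(B − 1)

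- B = 4: 2/3 = 67%
- B = 6: 3/5 = 60%

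Against 50% without the leak, that is a gain of 17 or 10 percentage points. Both block sizes are assumptions.

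**4. How often could the remaining arms become fully known?** Take B = 4 and the first two women disclosed. Only mecobalamin women have a stated reason for a doctor's call. P(both on mecobalamin) = (2/4) × (1/3) = 1/6. If each such woman leads to a call to the trial manager with probability q (assumption), the chance is q²/6, which is 1.5% at q = 0.3 and 4.2% at q = 0.5.

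**The case against.** The case against is substantial, and most of it limits the size of the point.

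- **The woman's own data are safe.** Her code is broken only after her last measurement, and the letter goes to her, not to the trial manager. This stands.
- **The leak needs a chain of events.** A mecobalamin woman must want to continue, her doctor must decide to call, and the doctor must choose the trial manager over the chief examiner. To use blocks, the trial manager must also know their size and boundaries, and an independent statistician generates the list. This stands, and it is why the information is partial.
- **Entry is protected.** A coexaminer shares the eligibility check, another approves final inclusion, and the chief examiner alone holds the closed envelopes. This stands and weakens any selection argument.
- **The primary outcome is not reached on the documents.** For the cold pressor test, "The participants end the test by raising their hands when they can no longer stand it", and no tester is named. This stands.

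A reader might infer more, namely that the blind as a whole is undone. All women are told of the sign of the active drug ("All participants are informed that their urine may turn red, which may occur during mecobalamin injections") while the comparator is plain saline ("Placebo substance is 2 mL sodium chloride (9 mg/ml), isotonic solution for parenteral use (Baxter) intramuscularly"), so a woman who sees red urine could infer her arm before week 12. The possibility is real, but the documents give neither how often the sign is noticed nor what guessing does to tolerance time. Supposing that 40–80% notice it and hold on 10 s longer gives 4–8 s, but that only restates the two suppositions. The article does plan related ratings: "The influence of expectation, desire for pain relief and pain variability will be measured before each injection". They are not arm guesses. That no guess question appears in the article does not show that none is planned, because the full protocol is not at hand.

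A reader might also infer that in one block of 4 in three the first two code breaks reveal the other two arms. That counts the both-placebo case, in which no doctor's call is expected. One in six is the ceiling, before allowing for whether calls are made at all.

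None of this removes the conflict between the letter's contact route and the statement that follows it.

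**Conclusion.** The point holds as an internal contradiction in Randomisation and allocation concealment: the letter opens a route that can defeat the trial manager's stated blind while that role is still dealing with other women. The documented exposure is assessor bias in algometry and in the interviews of later women. The documents do not show that the blind is undone, that the cold pressor result is biased, or that any given number of seconds is at risk.

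The size per disclosure is modest: a 67% or 60% chance that a given block-mate is in the opposite arm, instead of 50%. This rests on assumed blocks of 4 or 6 and on the trial manager knowing the block structure. The finding that others are still under test rests on the stated recruitment period and on roughly even entry. How often doctors would call the trial manager is unknown. The change is still worth making because the contradiction is plain and its removal costs almost nothing.

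**What to change.** 1. Name only the chief examiner, who is already in the letter, as the doctor's contact.
2. State that all doctors' queries go to the chief examiner until the last participant's third-visit measurement is complete.
3. Ask women in the letter not to tell the trial manager which treatment they had. They already know that contact from recruitment.

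The cost is about one line in the letter, with no added visits or staff.

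Optional, if the full protocol does not already have it: at week 12, before the stimulation tests, record each woman's guess of her arm and her reason for it (including urine colour) on a form that the trial manager does not see. Report it by arm as description only, because a guess at week 12 also reflects perceived benefit and so cannot cleanly separate unblinding from drug effect. This costs one extra question and leaves the information given about urine colour unchanged.

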### Adverse events (AES) and serious adverse events (SAEs)

AEs are defined as any unfavourable or unintended reaction occurring in a research person during the course of the study and where investigational medicinal products have been administered, regardless of dose. Any AE will be reported from day 1 of the study at each visit to the clinic and until the last visit made 24 weeks after the start of the study. All SAEs that occur during the course of the study will be reported to the sponsor within 24 hours of the research staff becoming aware of the incident. During the study, an annual safety report from the sponsor and responsible investigator is sent in to both the Swedish Medical Products Agency and the regional ethical review board.

### Statistical methods

The primary endpoint is tolerance time at cold pressor test and will be calculated on the difference between the two groups after 12 weeks and analysed by analysis of variance (ANOVA). Pain thresholds measured by pressure algometry test (Somedic) will be analysed using t-test and ANOVA, similar to the primary variable. Questionnaires (MPQ, RAND-36 and PGIC) will be analysed using Mann-Whitney tests. In cases of minor loss (less than 10%), a mixed model can be used as an alternative to t-test and ANOVA with repeated measurement. For variables with more than 10% loss, imputation of data will be used. Drop-out participants will be described in a specific analysis. Rejection analysis will be performed on the participants who interrupt the study prematurely.

Results will be reported for both intention-to-treat and per-protocol analyses. Intention-to-treat is defined as the participant is placed in the treatment group he or she had been randomised to. Per-protocol is defined as the participant is placed in the treatment group she de facto received and carried out without significant protocol deviations. The per-protocol results will be presented as sensitivity analyses. The participant may miss a maximum of two injections.

Self-reported ratings of desired and expected treatment outcome pretreatment and post treatment will be implemented in linear regression models to predict any of the outcome measures. Repeated ratings of desired treatment outcome, expected treatment outcome and pain variability will be calculated as each participant’s SD from the repeated ratings and implemented in a linear regression model to predict possible outcome measures.

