### Measurements

At the first measurement opportunity, the trial manager and coexaminer 1 carefully follow inclusion and exclusion criteria. Oral information is given again, and consent is signed by the participant and by coexaminer 1. First, the participant answers two questionnaires (short-form McGill Pain Questionnaire (MPQ)^27^ and RAND-36 (RAND-36 Health-Related Quality of Life)),^28^ then stimulation tests (cold pressor test and pressure algometry)^29–33^ are performed followed by pain rating (NRS)^34^ immediately after 1 min and after 3 min. Finally, blood samples for cobalamin (vitamin B_12_), kidney, liver and heart markers are taken. The participant provides an information card about the study’s design, purpose, treatment options and contacts with telephone numbers. The participant is asked about her interest in an interview in connection with the final measurement opportunity. Coexaminer 2 assesses the blood samples and approves the final inclusion. If tests deviate from accepted reference values, the participant is excluded and encouraged to seek medical attention.

After the approved inclusion, an independent chief examiner performs the randomisation. The participant then receives intramuscular injections of the active substance or placebo, once a week for 12 weeks, given by a registered nurse. Before each injection, the participant answers questions in which he or she estimate his or her expected effects of a given drug, desire for pain relief and average pain intensity during the past week (NRS). The participant has the opportunity to postpone the visit for ±3 days, for example, in case of illness or travelling and may miss a maximum of two injections in order to follow per-protocol analysis. Even if the participant is not compliant with the study protocol, the participant may retain the treatment regime for the duration of the study and may be analysed in the main intention-to-treat analysis.

The second measurement takes place after 12 weeks of intervention and three questionnaires (MPQ, RAND-36 and Patient Global Impression of Change (PGIC))^35^ are filled out. The stimulation tests cold pressor test and pressure algometry are performed as well as blood sampling of cobalamin/p (vitamin B_12_). In cases of low cobalamin/p, the participant is encouraged to seek medical attention but is still included in the study.

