### Outcomes

The primary outcome is tolerance time, maximised to 3 min, which is tested using the cold pressor test.

The secondary outcomes are

Pain experience measured by a pressure algometry test performed on the shoulder, hip, knee and elbow.Possible pain change measured by a pressure algometry test performed on the shoulder, hip, knee and elbow.Subjective experience of pain measured using NRS of 0–10, where 0 is the best outcome.Possible pain change measured using NRS of 0–10, where 0 is the best outcome.Ratings of expectation, desire for relief, using NRS of 0–10, where 0 is the best outcome.Ratings of expectation, pain variability, using NRS of 0–10, where 0 is the best outcome.Activity levels are assessed using MPQ Short Version score of 0–45.Quality of life is assessed using questionnaire RAND-36 score of 0–100.Experience of the effect of the drug, assessed using questionnaire PGIC score of 1–7.Control of vitamin B_12_ is done by measuring cobalamin in plasma.Qualitative in-depth interviews will be conducted to capture women’s lived experiences of pain, health, suffering and well-being.

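### The stated primary ANOVA at week 12 is valid but does not use the baseline cold pressor time; adjusting for it would gain precision at almost no cost

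*Protocol article*

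**What the plan says.** - **Primary outcome** (Outcomes): "The primary outcome is tolerance time, maximised to 3 min, which is tested using the cold pressor test".
- **Primary analysis** (Statistical methods): the endpoint "will be calculated on the difference between the two groups after 12 weeks and analysed by analysis of variance (ANOVA"). No baseline covariate, change score or time factor is named in that sentence.
- **Sample size**: "the expected effect difference is estimated at 20 s with an SD of 20 s between the two groups after 12 weeks of treatment". The method is given as "Using a two-sided t-test for two independent groups with a power of 80% and 5% significance level", and "it was calculated that each group would consist of 16 participants". This is raised to 20 per group to allow for loss.
- **Baseline data** (Measurements): at the first visit the participant completes MPQ and RAND-36, "then stimulation tests (cold pressor test and pressure algometry") follow, and randomisation comes later: "After the approved inclusion, an independent chief examiner performs the randomisation".
- **Other outcomes** (Statistical methods): pressure algometry is handled by t-test and ANOVA like the primary variable. "Questionnaires (MPQ, RAND-36 and PGIC) will be analysed using Mann-Whitney tests".
- **Repeated measures** (Statistical methods): the only mention is in the sentence on missing data, which allows a mixed model in place of t-test and repeated-measures ANOVA when loss is under 10%. It names no visits and no contrast.
- **Allocation** (Randomisation and allocation concealment): 1:1 in blocks. No stratification by baseline tolerance is described.

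**The concern.** With two arms and one time point, ANOVA is the independent-groups t-test on the week-12 value, which is also the test behind the sample size. Stable differences between women in cold tolerance then stay in the error term, although a pre-randomisation measurement could remove part of them. With 20 per arm and no stratification on it, baseline tolerance can also differ between arms by chance, and some of that difference carries into the estimated effect.

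What is at stake is precision, not validity. The article itself lists small numbers and heterogeneity of the fibromyalgia spectrum as limitations. The planned effect is a full standard deviation, so if the true effect is smaller, or the spread larger, the lost precision begins to matter.

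**Working it through.** **Inputs from the document.** Effect 20 s, SD 20 s, two-sided 5% level, 80% power, 16 per group calculated and 20 per group planned (Sample size).

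**Assumptions not in the document.** The baseline to week-12 correlation r, shown at 0.3, 0.5 and 0.7. A baseline SD of 20 s: the stated 20 s refers to the comparison after 12 weeks, and no baseline SD is given.

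**Step 1: the plan's own figure.** Normal approximation: n = 2 × (1.960 + 0.842)² × 20²/20² = 15.7, so 16 per group. The stated 16 reproduces. The exact t calculation needs 17 (power 78.1% at 16).

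**Step 2: the stated analysis at 20 per arm.** SE = 20 × √(2/20) = 6.32 s. With 38 df the 95% CI half-width is 2.024 × 6.32 = 12.8 s. Noncentral t power for 20 s is 86.9%, and the difference detectable with 80% power is 18.2 s.

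**Step 3: ANCOVA at 20 per arm.** Residual SD = 20 × √(1 − r²), with 37 df.

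| r | Variance removed (r²) | Residual SD | CI half-width | Power for 20 s | Detectable at 80% |
|---|---|---|---|---|---|
| unadjusted | – | 20.0 s | 12.8 s | 86.9% | 18.2 s |
| 0.3 | 9% | 19.1 s | 12.2 s | 89.8% | 17.4 s |
| 0.5 | 25% | 17.3 s | 11.1 s | 94.5% | 15.8 s |
| 0.7 | 49% | 14.3 s | 9.2 s | 99.1% | 13.0 s |

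These rows charge one degree of freedom but not the variance from estimating the slope. That variance is about 1/36, which multiplies the SE by √(1 + 1/36) = 1.014. The detectable differences become about 17.6, 16.0 and 13.2 s, and power 89.0%, 93.9% and 98.9%.

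If r were 0, the unadjusted 86.9% would become 86.8% with the degree of freedom alone and 85.9% with the slope included. The worst-case price is about one percentage point.

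**Step 4: chance imbalance.** With a baseline SD of 20 s, the baseline mean difference has SE 20 × √(2/20) = 6.3 s, and about 32% of randomisations give an imbalance at least that large. With equal SDs, the expected shift in the unadjusted estimate is r × imbalance: 0.3 × 6.3 = 1.9 s, 0.5 × 6.3 = 3.2 s, 0.7 × 6.3 = 4.4 s.

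**Step 5: would repeated-measures ANOVA settle it?** On baseline and week 12, its group-by-time test equals a change-score analysis with SD 20 × √(2(1 − r)) = 23.7 / 20.0 / 15.5 s. Power for 20 s is 74.0% / 86.9% / 97.8%. That is below the unadjusted test at r = 0.3, equal to it at r = 0.5, and below ANCOVA at all three values.

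**The case against.** **The unadjusted comparison is not an error.** Over all randomisations it is unbiased, its type I error is 5%, and it matches the sample-size basis. This stands in full. A reader might infer that the analysis is invalid or the trial underpowered; the document supports neither, since power is about 87% on the plan's own figures.

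**The gain depends on an unstated r.** This stands. At r = 0.3 it is modest: about 3 points of power and 0.8 s in the detectable difference.

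**Imbalance passes into the estimate only in part.** A reader might take a 6.3 s imbalance as a 6.3 s shift, about a third of the planned effect. The expected carry-over is r times the imbalance, so 1.9 to 4.4 s over the range shown.

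**Repeated measures might already bring in baseline.** The wording leaves some doubt, but it sits in an optional missing-data provision and specifies neither visits nor contrast. A reader might go further and infer that the test will be a group main effect averaged over visits, which would dilute the week-12 effect. Nothing in the document specifies that test, and the stated target is the difference after 12 weeks.

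**For MPQ and RAND-36, lack of adjustment is an inference.** The article does not say whether the Mann-Whitney test is applied to week-12 scores or to changes. This stands, so the point on the questionnaires is secondary.

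**A fuller protocol or analysis plan may name covariates.** Possible, but the article states a primary method and does not defer the choice.

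**Conclusion.** The point holds as a recommended improvement in efficiency, not as a flaw in validity. On its plain reading, the stated primary analysis leaves out a baseline measurement that the trial already takes before randomisation. At 20 per arm, and under the plan's 20 s effect and SD, adjustment would narrow the 95% CI half-width from 12.8 s to between 12.2 and 9.2 s for r from 0.3 to 0.7, slightly less once slope estimation is counted. It would also limit the effect of chance imbalance on the estimate. These sizes rest on the assumed r, on a baseline SD of 20 s for the imbalance figures, and on a linear model for an outcome capped at 180 s, whose effect has not been examined here. The mention of repeated-measures ANOVA does not remove the point, because the change-score test it would imply is less efficient than ANCOVA over this range.

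**What to change.** In Statistical methods, state the primary analysis as ANCOVA: week-12 tolerance time on arm plus baseline tolerance time, reporting the adjusted between-group difference with its 95% CI. Keep the unadjusted ANOVA as a sensitivity analysis, and add a check of how the 180 s cap affects the linear model.

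Use the same model for pressure algometry. For MPQ and RAND-36, baseline adjustment is preferable. PGIC has no baseline and can stay with the Mann-Whitney test. State which visits and which contrast any repeated-measures or mixed model would use.

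The cost is a sentence or two of text and one degree of freedom, with no new data or visits. If baseline proved uninformative, the loss would be about one percentage point of power. The model should be fixed before outcomes are analysed by arm, so that its choice cannot follow the result.
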